### Phase 2: Pilot Trial

#### Overview

We will conduct a wait-list control trial, where participants are randomized upon enrollment to either an immediate intervention or a delayed intervention (wait-list control) condition, in which they receive the intervention after a 2-month waiting period. We chose this design to protect the ethical treatment of participants by ensuring that everyone will have access to a potentially impactful intervention after a short waiting period [28,29].

#### Participant Experience

For phase 2, we will recruit a total of 60 participants. Inclusion criteria include (1) Ethiopian and/or Eritrean origin; (2) age 18‐29 years (consistent with Arnett’s conceptualization of emerging adulthood [30], and community priorities); (3) residence in the Atlanta area; and (4) ability to read and comprehend English. Eligibility will be assessed via a brief screener survey, which will be self-administered remotely (eg, if responding to a social media advertisement) or on a tablet by study staff (if recruited in-person). Study participants will be recruited using multiple approaches, including CBO and student organizations, YAB referrals, social media recruitment, and venue-based recruitment at community cultural events. Study team members will contact those who express interest for an initial enrollment meeting. During this initial Zoom meeting, a study team member will conduct a one-on-one informed consent discussion before enrolling participants. During the consent procedure, the research team will detail the intervention components and address any inquiries raised by the participant. The team will also outline the potential risks and harms associated with participation in this study, including possible unpleasant or uncomfortable experiences during group activities with other Ethiopian and Eritrean youth, as well as the risk of a breach of confidentiality. Measures will be implemented to ensure that personal information remains confidential and is not accessible to individuals outside the research team; this includes using passwords and encryption to secure digital study files. Physical documents will be stored in a locked file cabinet accessible solely to the research team. However, if a study participant discloses personal information during the group session, there is a possibility that other participants will share it outside the session. The consent process will be completed electronically using RedCap (Research Electronic Data Capture) [31]. After the initial study overview walkthrough, the study team will share the consent form with the participant via Zoom chat or email, depending on the participant’s preference. The participant will have the opportunity to review the consent documents and ask any questions before signing the electronic consent form provided through RedCap. A signed copy of the consent form will be sent to participants for their records. Participants will also complete a baseline survey (measuring risk factors, resilience processes, and mental health outcomes) and will then be randomly assigned to either the immediate or delayed intervention group. We will recruit and enroll continually until we accrue groups of 16 individuals. Within these groups, we will randomly assign half (n=8 people) to the immediate intervention and half (n=8 people) to the delayed intervention condition. This process will be repeated until we reach our overall recruitment goals.

Participants will attend a 2-hour group session once per week for 8 weeks. The first and final sessions are designed to be delivered in person, while the remainder is to be delivered via Zoom videoconference. A total of 2 or 3 trained PFs will lead sessions. The structure, duration, and length of the program were designed by the study team together with the YAB and also reflect previous group interventions developed for other immigrant groups [15,16,18]. Sessions will include psychoeducation, engaging, interactive activities (eg, case-scenario discussions and trivia games), and practice of coping skills (Table 1). Participants will complete a session evaluation form each week and receive US $25 payment on an electronic gift card. All participants will be provided with a mental health resource guide featuring affordable services verified and compiled for Ethiopian and Eritrean youth in Atlanta. After completing the program, participants will receive links to follow-up surveys at 2, 4, and 6 months, and a subset will take part in qualitative interviews.

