### Data Collection

We will use REDCap [31] to create and allow self-administration of surveys measuring background factors, resilience processes, and mental health outcomes at baseline 2-, 4-, and 6-month time points (Table 2). Surveys will primarily be completed remotely but can be done in person if a participant prefers. We estimate that completing each survey will take approximately 30 minutes. We will use best practices for web-based data collection to detect suspicious response patterns [43]. Upon completing the survey, respondents will receive US $25. Short postsession participant and facilitator surveys will capture satisfaction and challenges with each session. In addition to the survey measures outlined in Table 2, the study team will conduct a fidelity check at each session to ensure that each session closely follows the intervention design. We will use a participant attendance and engagement tracker to monitor participants’ engagement throughout each session closely.

**Table 2. T2:** Survey measures.

Construct	Measure	Description	Number of items and examples	Response format
Relationships and roles	Multidimensional scale of perceived social support	Questionnaire measuring support system	12 items; eg, “There is a special person who is around when I am in need. Or my family really tries to help me.”	7-point Likert scale
Cultural and community factors	Phinney’s multigroup ethnic identity measure	Questionnaire measuring ethnic identity feeling or reaction	12 items; eg, “I have a clear sense of my ethnic background and what it means for me. Or I am active in organizations or social groups that include mostly members of my own ethnic group.”	4-point Likert scale
Subjective psychological well-being	General well-being	Questionnaire measuring subjective psychological well-being and distress	24 items; eg, “In the past month; how have you been feeling in general? Or, during the past month, have you been bothered by nervousness or your nerves?”	Likert scale and 6-point and 10-point scales
Knowledge, beliefs, and attitudes	Mental health knowledge, beliefs, attitudes, and coping strategies (MHLqSVa^a^)	Questionnaire measuring mental health knowledge, beliefs, and attitudes	16 items; eg, “Mental disorders do not affect people’s behavior. Or mental illness is a sign of personal weakness.”	5-point Likert scale

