### Statistical Analysis

We will conduct descriptive analysis to assess the acceptability, feasibility, and safety of Weyera. To evaluate the acceptability of the intervention, descriptive quantitative analyses of the intervention data will focus on tabulating and summarizing the results of the postsession satisfaction survey measures. To determine feasibility, we will monitor recruitment rates, effort required (eg, staff hours), number of screenings, and the proportion of eligible participants who agree to enroll. We will summarize rescheduled, canceled, and missed sessions to help estimate staffing needs and retention protocols for a future full trial. Additionally, we will compare the characteristics of participants lost to follow-up with those who remain to identify any systematic patterns that may affect the results. Safety will be assessed by tabulating and describing any adverse events during study participation.

Additionally, we will measure mental health outcomes, hypothesized moderators, and background (risk) factors to evaluate the feasibility of data collection (eg, time to complete surveys), as depicted in Table 1. To analyze changes over time, we will plot means and proportions from baseline to follow-ups. Exploratory hypotheses will be evaluated using linear mixed models, estimated via maximum likelihood, and fitted to provide all necessary information for analyses typical of a full randomized controlled trial [44]. We will also assess the feasibility of interaction analyses (for effect modification). As of March 2026, the study has enrolled 65 participants (33 in the intervention group, 32 in the control group) who have completed the baseline survey. We have not started data analysis.

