### Limitation and Future Directions

This randomized wait-list control trial is designed to minimize bias. Beyond the study team, participants remain unaware of their specific group assignment; they are only notified of the start dates for their respective group sessions. Sessions for both the immediate and wait-list groups are designed and implemented identically. Nevertheless, this methodology does not entirely eliminate potential selection bias, given the inherent challenges associated with this study design, in which the wait-list group may be prone to higher dropout rates due to the interval between enrollment and the start of the intervention. Furthermore, varying expectations among participants may affect their motivation to fully engage with the intervention following the waiting period. In addition, the presurvey and postsurvey measures are self-reported by study participants, which can introduce biases due to reduced accuracy and potential social desirability bias.

Upon the conclusion of this trial, in collaboration with the CBOs, the team will conduct webinars to present our qualitative and quantitative findings. In addition, further dissemination will include scientific and academic journal publication and conference presentations. Building upon the findings of this research, the subsequent objective of the project is to undertake a statistically powered trial designed to evaluate the efficacy of the intervention in addressing the mental health needs of Ethiopian and Eritrean immigrant youth.

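### One section ties follow-up survey links to finishing the program and another sets no such condition; the plan should say that everyone randomised is surveyed on fixed dates

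*Protocol article*

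**What the plan says.** The Participant Experience section has the only sentence that says when follow-up links go out and to whom: "After completing the program, participants will receive links to follow-up surveys at 2, 4, and 6 months". It does not define completion. The Data Collection section gives the schedule as "mental health outcomes at baseline 2-, 4-, and 6-month time points (Table 2". It attaches no attendance condition, but it does not say that every randomised person is surveyed either.

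The design around these sentences is clear. Every participant fills in a baseline survey before assignment. The program runs as follows: "Participants will attend a 2-hour group session once per week for 8 weeks". The delayed arm is a condition "in which they receive the intervention after a 2-month waiting period".

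On attrition, the limitations section says that "the wait-list group may be prone to higher dropout rates due to the interval between enrollment and the start of the intervention", and the Statistical Analysis section says "we will compare the characteristics of participants lost to follow-up with those who remain to identify any systematic patterns". No dropout or completion rate is stated.

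**The concern.** Completing the program is an event after randomisation. If it triggers the survey links, then whether a person has any follow-up data depends on behaviour that allocation can influence. The article itself raises the possibility of more dropout in the wait-list arm. Someone who stops after a few sessions, or who is wait-listed and never attends, would contribute a baseline value and nothing more. A maximum-likelihood mixed model cannot repair that if stopping is related to the later, unobserved outcome.

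The main aims are touched as well. The Sample Size and Power section says that the sample serves to try out data collection and the means of recruiting and keeping participants. A full trial needs to know what share of randomised people return a survey when they are sent one. A completion trigger turns leaving the sessions into a missing survey automatically, so the comparison of lost and retained participants would mix the uninvited with the non-responders.

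Finally, a wait-list design gets its untreated comparison from assessments made before the delayed arm starts. A trigger on completion removes them.

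**Working it through.** There is no figure in the plan to reproduce. The target of 60 was explicitly not derived from an effect size, and no retention or completion rate is given. The check therefore sets the sections side by side, does the calendar arithmetic, and adds an illustration on assumed rates.

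**1. Who is sent a follow-up survey**

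| Participant | Participant Experience, read literally | Data Collection |
|---|---|---|
| Immediate arm, finishes | yes | 2, 4, 6 months |
| Either arm, stops part-way | none after baseline | 2, 4, 6 months |
| Wait-listed, never starts | none after baseline | 2, 4, 6 months |
| Wait-listed, finishes | none until sessions end | 2, 4, 6 months |

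The right-hand column assumes that the schedule applies to everyone, which the section does not say.

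**2. When the surveys fall**

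Inputs: wait of 0 or 2 months; program of 8 weeks = 56 / 30.4375 = 1.84 months; surveys at 2, 4 and 6 months. Assumption: sessions start at enrolment, or directly after the wait.

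Months from enrolment, if counted from completion = wait + 1.84 + survey month:

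- Immediate: 3.84, 5.84, 7.84
- Delayed: 5.84, 7.84, 9.84

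The Results section places phase 2 data collection between September 2025 and April 2026, which is at most 8 months. The delayed arm's last survey (9.84) cannot fit. The immediate arm's last survey (7.84) fits only for someone who started in the first 8 − 7.84 = 0.16 months, about 5 days. Counted from baseline, the last survey falls at 6 months and fits for anyone enrolled by about the end of October 2025.

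Suppose instead that months are counted from baseline but links are still released on completion. The delayed arm completes at 2 + 1.84 = 3.84 months, after its 2-month date has passed. Under either origin, a completion trigger gives that arm no survey before its sessions.

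**3. How many people could be affected (assumed rates)**

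Enrolled: 33 immediate, 32 delayed. People due a follow-up survey = n × (1 − d), where d is the assumed proportion not completing:

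- d = 10% in both arms: 29.7 and 28.8
- d = 20%: 26.4 and 25.6
- d = 30%: 23.1 and 22.4
- 15% immediate, 30–40% delayed: 33 × 0.15 = 4.95 plus 32 × 0.30 = 9.6 to 32 × 0.40 = 12.8, so about 15–18 of 65 with no follow-up

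**4. Possible bias in an arm contrast (assumed rates and gaps)**

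If completers and non-completers differ by g SD, the mean among completers is off by d × g. With the same g in both arms, and no help from baseline data, the contrast is off by the difference in d times g:

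- equal d: 0
- (0.30 − 0.15) × 0.5 = 0.075 SD
- (0.40 − 0.15) × 0.5 = 0.125 SD
- (0.40 − 0.10) × 0.8 = 0.24 SD

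If g differs by arm, equal d no longer gives zero: with d = 0.20 and gaps of 0.5 and 0.25, the bias is 0.10 − 0.05 = 0.05 SD.

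**The case against.** The strongest reply is that the sentence sits in a narrative of the expected participant path, where the opening words read naturally as a time marker. The word 'only' is not there, completion is not defined, and the section that sets out data collection has no such condition. The calendar supports this: surveys counted from completion do not fit the stated window, which suggests loose phrasing and not a deliberate eligibility rule. Much of this stands, and it is why the point is put as two sections to reconcile.

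A reader might infer that people who stop have no outcome data at all, or that the trial will compare completers only. The documents support neither. Mental health outcomes are measured in everyone at baseline. No completers-only analysis set is defined, and the planned models are mixed models by maximum likelihood, described as exploratory.

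A reader might also infer that adherence and retention cannot be separated. Session attendance is in fact logged on its own, and the analysis section plans a summary of sessions missed, moved or called off. The comparison of lost and retained participants remains possible from baseline data. What it could not do under a completion trigger is distinguish those never sent a survey from those who did not answer, unless invitation status is also recorded.

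On dropout, the limitations section calls higher loss in the wait-list arm possible, not expected. The bias figures are also not estimates for a treated-versus-untreated contrast, because under the literal reading both arms have had the program by every follow-up.

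Follow-up of people who stop sessions may be described in a fuller document, and silence alone would be no fault. This is not silence: the article states a trigger, and surveys that were never sent cannot be recovered by a later analysis plan.

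**Conclusion.** The point holds as a conflict in wording with practical consequences. The one sentence that governs sending the links ties them to completion; the schedule elsewhere does not. If staff follow the former, non-completers get no follow-up survey, and the wait-list arm gets none before its sessions even with full attendance. The second result needs no assumption about dropout, only the stated 2-month wait and 8-week program.

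The effect on the exploratory outcomes cannot be sized from the document. The illustrations run from 0 to 0.24 SD and rest wholly on assumed rates and gaps. They show what would matter, namely unequal non-completion and non-completers who differ, not what will happen. If the team already surveys everyone on fixed dates, only the text needs correcting. The change is worth making because it protects both the as-randomised comparison and the survey-retention figure that a later full trial would use.

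**What to change.** Replace the sentence in Participant Experience, and align Data Collection with it, along these lines: *Every randomised participant, whatever their session attendance, will be sent the 2-, 4- and 6-month surveys on fixed dates counted from [baseline or randomisation], unless they withdraw from data collection.*

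- Choose one time origin and use it in both arms. The last immediate session falls only about 5 days before 2 months (2 − 1.84 = 0.16 months) if sessions start at once, and the delayed sessions begin at about 2 months. State that the 2-month survey is due before the first delayed session.
- Record stopping sessions and withdrawing from surveys as separate statuses, and log whether each survey was sent.
- Report survey completion by arm with all randomised as the denominator, apart from the session attendance already tracked.

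The cost is a REDCap scheduling change, from completion to date, and US $25 for each extra survey returned. That is at most 3 × 25 = US $75 per person who would otherwise not be surveyed; for the assumed 15–18 people, US $1,125 to 1,350. As of March 2026 analysis had not started, so surveys not yet due at that point could still go to people who had stopped attending.

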### Sample Size and Power

The goals of this study are to assess feasibility, acceptability, and safety. The proposed sample size of 60 participants was not derived based on estimating effect size estimates (which are often unreliable from small pilot studies [32-41]), but to provide a sufficiently large sample to obtain reasonable descriptive data and to pilot test our data collection procedures, intervention manual, and recruitment and retention methods, in anticipation of a future fully powered efficacy trial. The qualitative sample size is based on Kvale’s estimate that 15±5 individuals are typically sufficient to reach thematic saturation [42].

### Data Collection

We will use REDCap [31] to create and allow self-administration of surveys measuring background factors, resilience processes, and mental health outcomes at baseline 2-, 4-, and 6-month time points (Table 2). Surveys will primarily be completed remotely but can be done in person if a participant prefers. We estimate that completing each survey will take approximately 30 minutes. We will use best practices for web-based data collection to detect suspicious response patterns [43]. Upon completing the survey, respondents will receive US $25. Short postsession participant and facilitator surveys will capture satisfaction and challenges with each session. In addition to the survey measures outlined in Table 2, the study team will conduct a fidelity check at each session to ensure that each session closely follows the intervention design. We will use a participant attendance and engagement tracker to monitor participants’ engagement throughout each session closely.

**Table 2. T2:** Survey measures.

Construct	Measure	Description	Number of items and examples	Response format
Relationships and roles	Multidimensional scale of perceived social support	Questionnaire measuring support system	12 items; eg, “There is a special person who is around when I am in need. Or my family really tries to help me.”	7-point Likert scale
Cultural and community factors	Phinney’s multigroup ethnic identity measure	Questionnaire measuring ethnic identity feeling or reaction	12 items; eg, “I have a clear sense of my ethnic background and what it means for me. Or I am active in organizations or social groups that include mostly members of my own ethnic group.”	4-point Likert scale
Subjective psychological well-being	General well-being	Questionnaire measuring subjective psychological well-being and distress	24 items; eg, “In the past month; how have you been feeling in general? Or, during the past month, have you been bothered by nervousness or your nerves?”	Likert scale and 6-point and 10-point scales
Knowledge, beliefs, and attitudes	Mental health knowledge, beliefs, attitudes, and coping strategies (MHLqSVa^a^)	Questionnaire measuring mental health knowledge, beliefs, and attitudes	16 items; eg, “Mental disorders do not affect people’s behavior. Or mental illness is a sign of personal weakness.”	5-point Likert scale
Depression symptoms	Patient health questionnaire-9	Screen for depression, measure its severity, and monitor treatment responses	9 items; eg, “Little interest or pleasure in doing things or feeling down, depressed, or hopeless.”	4-point scale
Anxiety symptoms	Generalized anxiety disorder-7	Questionnaire used to assess the severity of generalized anxiety disorder	7 items; eg, “Worrying too much about different things or feeling nervous, anxious, or on edge.”	4-point scale
Resilience	Brief resilience Scale	Questionnaire measures an individual’s ability to recover from stress	6 items; eg, “I have a hard time making it through stressful events or I usually come through difficult times with little trouble.”	5-point Likert scale
Trauma experiences	Posttraumatic stress disorder checklist (PCL)	Questionnaire used to screen and monitor PTSD symptoms	20 items; eg, ”Avoiding memories, thoughts, or feelings related to the stressful experience? Or trouble remembering important parts of the stressful experience?”	5-point scale
Stigma	Personal and perceived stigma (unvalidated questionnaire)	Questionnaire used to assess how others perceive people with mental health issues	15 items; eg, “Most people believe that a person who has received mental health treatment is as intelligent as the average person or most people feel that receiving mental health treatment is a sign of personal failure.”	6-point Likert scale
Stigma	Self-stigma of seeking help scale-3 (ultra-brief)	Questionnaire assessing reaction to a situation	3 items; eg, “It would make me feel inferior to ask a therapist for help. Or if I went to a therapist, I would be less satisfied with myself.”	5-point Likert scale
Coping strategies	Mental health behaviors (unvalidated questionnaire)	Questionnaire assessing coping strategies practiced in sessions	12 item; eg, “In the past 2 month how often have you used journaling to deal with stress or mental health distress?”	5-point Likert scale
Alcohol and drug use	NIAAA^b^ and DAST-10^c^	Self-reported use of consumption of alcohol and other substances	14 items; eg, “During the last month, on how many days did you have any kind of drink containing alcohol? By a drink we mean half an ounce of absolute alcohol (eg, a 12 ounce can or glass of beer or cooler, a 5-ounce glass of wine, or a drink containing 1 shot of liquor.)”	Yes or no
Self-efficacy	The general self-efficacy Scale, adapted	Questionnaire assessing confidence in ability to solve problems	10 items; eg, “I can always manage to solve difficult problems if I try hard enough.”	4-point Likert scale

a MHLqSVa: Mental Health Literacy questionnaire—short version for adults.

b NIAAA: National Institute on Alcohol Abuse and Alcoholism.

c DAST-10: Drug Abuse Screening Test.

